## Statistical methods

### Statistical methods for primary and secondary outcomes {20a}

#### Description of statistical methods

Primary endpoint data will be presented for each arm separately, and the primary analysis will be a logistic regression model, with adjustment for donor organ type (DCD/DBD) to assess whether there is a statistically significant difference between treatment arms. An additional analysis where the model is adjusted for transplant centre will also be considered given sufficient counts within centre. The additional model will employ Firth’s penalised maximum likelihood to mitigate for small sample bias and overfitting. This analysis will include all livers randomised in an intention-to-treat (ITT) analysis. The proportion of livers actually transplanted will be presented and analysed in a similar way. A modified intention-to-treat analysis (mITT) will be considered for livers that were randomised but were not subsequently perfused. Reasons for not undergoing perfusion will be documented and an independent adjudication panel will consider inclusions to a mITT analyses after consideration of these reasons, on a case-by-case basis. There may be indirect logistical reasons rendering the inclusion of non-perfused livers to an ITT inappropriate, i.e. these reasons are not completely unrelated to the allocated intervention.

Many of the secondary endpoints are only relevant for livers that are actually transplanted, and so these analyses will be conducted on a modified intention-to-treat (mITT) population of all livers randomised and transplanted, analysed according to randomised treatment. Outcomes will be presented as counts and proportions, means and standard deviations, or medians and interquartile ranges as appropriate and analysed using linear regression for continuous outcomes; logistic regression for binary outcomes; and Cox regression analysis for time to event outcomes. In addition to the peak ALT/AST in the first 7 days post-transplant, the area under the curve will be used summarise the post-operative biochemical markers (ALT, AST, GGT, INR and bilirubin) levels over time. There will be very limited statistical testing of secondary endpoints in this small trial, and the focus will be on presenting the effect size of the defatting + NMP intervention relative to standard NMP with 95% confidence interval to help inform the design of a future definitive trial.

An ITT analysis will be performed for the primary outcome and secondary (donor liver related) outcomes. Secondary (recipient) outcomes will be analysed using a mITT approach. This analysis will exclude livers perfused but not transplanted for any reason.

For the mechanistic work, measures will be compared before and after perfusion to assess for a change during machine perfusion. A paired *t*-test will be used to compare the means of these levels pre- and post treatment to determine whether any change is statistically significant. For all analyses with statistical testing, a *p*-value of < 0.05 will be used to determine statistical significance.

Full details of the statistical analysis plan will be made available on the ISRCTN registry webpage (ISRCTN 14957538: 10.1186/ISRCTN14957538).

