### Sample size {14}

Our preliminary data described above showed that 40% more livers met functional criteria for transplantation where NMP was combined with defatting versus NMP alone (100% vs.60%) [33]. However, this is based on a small sample size and the interventions were tested on a very high-risk group of livers that had all been previously discarded. Using the proposed inclusion criteria, a smaller effect size is anticipated. Whilst the present study is not primarily intended to demonstrate efficacy, a sample size of 60 livers (30 per group) will provide greater than 80% power to detect a difference of 30% (from 65% in the control NMP arm) in those meeting criteria for transplantation (at 5% significance): this is a clinically significant outcome. This sample size should provide sufficient information for the design of a larger, phase III study to formally test the efficacy of the intervention.

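### Firth's penalised likelihood is assigned only to the optional centre-adjusted model, although at the design rates the primary logistic model has a 21% chance of giving no finite odds ratio

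*Protocol article*

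**What the plan says.** Under Statistical methods for primary and secondary outcomes {20a}, the protocol article states that "the primary analysis will be a logistic regression model, with adjustment for donor organ type (DCD/DBD". It does not say how this model is fitted, or whether the treatment effect is tested by a Wald, likelihood-ratio or score statistic. A second model that adjusts for transplant centre will be considered if counts per centre allow. For that model alone an estimator is named: "The additional model will employ" Firth's penalised likelihood, with small-sample bias and overfitting given as the reasons. The proportion of livers transplanted is to be analysed in a similar way to the primary endpoint. The section ends by referring to the SAP for full details.

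Under Sample size {14}, 30 livers per group "will provide greater than 80% power to detect a difference of 30% (from 65% in the control NMP arm", at 5% significance. No test is named there either. The same section reports preliminary results of 100% versus 60%, warns that they come from a small, very high-risk set of discarded livers, and expects a smaller effect in this trial.

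**The concern.** The article recognises a small-sample problem and applies the remedy to the model that may never be fitted, not to the one that carries the primary result. Read 30% as an absolute difference, so that the planned rate in the defatting arm is 95%. With 30 livers, that arm is expected to have 30 × 0.05 = 1.5 failures, and none is a realistic outcome. An unpenalised logistic model then has no finite treatment estimate, with or without donor type in the model.

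Two things are at stake. The first is the reported effect: the closer the intervention comes to full success, the more likely the primary odds ratio is to be infinite, with no Wald interval. The second is the test: a Wald p-value in such a trial is close to 1 even when the result strongly favours treatment. For example, 30/30 versus 20/30 has a Fisher p of 0.0008, yet the Wald test could not reject. Choosing a remedy after seeing an arm with no failures would make the primary analysis depend on the data.

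**Working it through.** **Inputs.** From Sample size {14}: n = 30 per arm, control rate 0.65, difference 0.30 (so 0.95 with defatting), 5% significance. From the statistical methods section: significance is judged by "a *p*-value of < 0.05 will be used to determine statistical significance". Assumptions: two-sided test, absolute difference, all 30 livers per arm evaluable.

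**The plan's own figure.** Two-proportion formula with pooled variance under the null:
- pooled rate (0.65 + 0.95)/2 = 0.80; null SE = √(2 × 0.80 × 0.20/30) = 0.1033
- alternative SE = √((0.65 × 0.35 + 0.95 × 0.05)/30) = 0.0957
- power = Φ((0.30 − 1.96 × 0.1033)/0.0957) = Φ(1.02) = 84.6%

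The stated figure of more than 80% is reproduced; 27 per arm would give 80% by the same formula.

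**Chance of an arm with no failures.** P(30/30) = p^30:
- p = 0.90: 4.2%
- p = 0.95: 21.5%
- p = 0.97: 40%
- p = 0.98: 55%

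**Power by test, unadjusted model.** All 31 × 31 outcomes were enumerated at 0.65 versus 0.95. Tables with an empty failure cell count as non-rejections for Wald, because the standard error diverges.

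| Test | Power |
|---|---|
| Wald | 62.7% |
| Score (uncorrected chi-square) | 88.0% |
| Likelihood ratio | 89.8% |

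The Wald test misses 100 − 62.7 = 37.3% of trials. Tables with an empty cell make up 21.5/37.3, or somewhat over half, of these. The large-sample Wald formula can be checked by hand. The log odds ratio is 2.944 − 0.619 = 2.325, and its SE is √(1/(30 × 0.2275) + 1/(30 × 0.0475)) = 0.921. So power = Φ(2.325/0.921 − 1.96) = 71%. Even without allowing for empty cells, this is below 80%.

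**Power with adjustment for donor type.** Simulation, 5,000 trials per scenario. The article gives no donor-type split, so 15/15 and 20/10 per arm were assumed, and in one scenario success rates also differed by donor type.

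| Test | Power across scenarios |
|---|---|
| Maximum likelihood, Wald | 63–65% |
| Maximum likelihood, likelihood ratio | 89–90% |
| Firth, Wald | 80–82% |
| Firth, penalised likelihood ratio | 87–88% |

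A separate simulation (4,000 trials, 40% DCD assumed) gave 63%, 89% and 87% for the first, second and fourth rows.

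**Type I error, adjusted model, 65% in both arms:** Wald 4.6%, likelihood ratio 5.4%, Firth Wald 4.0%, Firth penalised likelihood ratio 4.8%. The separate simulation gave 4.5% for the Firth penalised likelihood ratio at 65%, and 4.2% at 80% in both arms.

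**The case against.** A reader might infer that the article specifies an ordinary maximum likelihood fit with a Wald test, and that its power is therefore 63% and not above 80%. The documents do not support this. No estimator is named for the primary model; an unpenalised fit is inferred only from the contrast with the centre-adjusted model. No test is named at all. On the same unpenalised model, the likelihood-ratio and score tests both exceed 80%, and only Wald falls short. The SAP, which is not shown, may name the test, and that is a detail commonly left to it.

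A reader might also infer that an arm without failures would leave no usable p-value and no effect size for planning phase III. That goes too far. A likelihood-ratio p-value and a finite lower profile-likelihood bound would still exist. The article also says that primary endpoint data will be shown for each arm, so the two proportions and their difference remain finite even at 30/30.

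The 21% belongs to the design alternative. The sponsor expects a smaller effect than in the preliminary data, and at a true 90% the chance is 4%. The trial is also described as not primarily intended to show efficacy.

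All of this stands, and it limits the point. It does not remove it. The article does allocate the small-sample method, and places it only on the optional model. Naming a different test in the SAP would secure the p-value but would not make the maximum likelihood odds ratio finite.

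**Conclusion.** The point holds as a worthwhile improvement. At the article's own design rates, about one trial in five would give an infinite odds ratio, with no Wald interval, from an unpenalised primary model; at a true 90% it would be about one in 24 (1/0.042). The power statement is not shown to be wrong: it is met by two of the three standard tests of the model and missed, at about 63%, only by Wald.

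This rests on a two-sided 5% level, an absolute 30-point difference, 30 evaluable livers per arm, and, for the adjusted figures, assumed donor-type splits. The results varied little across the splits tried. That the primary fit is unpenalised is an inference from the text, and that Wald would be used is a condition, not something the article states.

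**What to change.** - Fit the primary model (treatment and donor type) by Firth's penalised likelihood, with a penalised profile-likelihood p-value and 95% confidence interval. Use the same model for the proportion of livers transplanted.
- Report the donor-type-standardised risk difference with a 95% confidence interval beside the odds ratio. It is finite at 30/30 and is on the scale of the sample-size statement.
- Tie the power statement to this test: about 87% at 65% versus 95%.
- Settle this before outcome data by arm are seen.

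The cost is a few sentences in the protocol or SAP and a restated power figure. No extra livers are needed, and the method is already planned for the additional model. The downside is about 2 to 3 points of power compared with the unpenalised likelihood-ratio test (87–88% against 89–90%). In return, simulated type I error is 4.2–4.8% instead of 5.4%, and the estimate is always finite. Keeping the unpenalised fit with a likelihood-ratio test would protect the power but not the estimate.

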### Concealment mechanism {16b}

Donor organs meeting enrolment criteria will be randomised, using a 1:1 allocation ratio, using permuted blocks of varying undisclosed size and will be stratified by donor organ type (DCD/DBD). The randomisation list will only be accessible to the trial statisticians and sealed envelope. Randomised livers that are not perfused due to unforeseen reasons will not be replaced. It is anticipated that non-perfusion of a randomised liver will be a very uncommon event.

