### Methods in analysis to handle protocol non-adherence and any statistical methods to handle missing data {20c}

#### Procedure for accounting for missing, unused, and spurious data

Withdrawals from the trial after implantation will be documented, and a narrative analysis of withdrawals will be performed. Recipients withdrawing from the trial after implantation will be included in analysis using all available data. Consideration will be given to model-based and multiple imputation methods and detailed in the SAP. The rational for this is briefly described below.

The primary outcome will be available for all livers randomised and perfused. Missing data will be described and reported, although it is anticipated very few patients will be lost to follow-up. The reason for missingness for variables implicated in the primary analyses will be explored through regression of the missing variable indicator on other observables and detailed in the SAP. All analyses will include all data available.

The small sample size poses significant limitations for building robust multiple imputation models for handling missing data. Consideration of multiple imputation model will be given only for the analyses of selected/primary outcomes when it is valid to do so:The proportion of missing data is less than 5% and the impact of missing is negligibleWhen no additional information can be obtained (no auxiliary variables to use for imputation can be identified)When missing data can be assumed to be missing completely at random from the outsetWhen missingness can be assumed missing at random conditional on other observable data

In the case where the primary outcomes are not missing at random, then a ‘worst-best-case’ scenario sensitivity analyses will be undertaken to show the range of uncertainty due to missing. Briefly, in such analyses, a ‘worse-best-case’ scenario dataset will be generated where it is assumed that all participants missing the primary outcome in one group had a harmful outcome and all missing the outcome in the other group had a beneficial outcome.

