### Frequency and plans for auditing trial conduct {23}

The investigators shall conduct this study in accordance with this protocol and any conditions of approval/notification imposed by the Research Ethics Committee and Competent Authority. Failure to comply with and/or inability to meet these regulations may jeopardise further participation of the investigator or investigative site in this and future clinical studies.

A ‘protocol deviation’ is a failure to adhere to the requirements specified in this study protocol without adequate justification. Examples may include the enrolment of a liver or recipient not meeting all of the inclusion/exclusion criteria specified in section 8 or missed study procedures without documentation. Livers excluded after randomisation due to factors not known at the time of randomisation (see procedures for reporting adverse events) will not be deemed protocol deviations.

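### The condition for leaving a non-perfused liver out of the ITT is worded the wrong way round and contradicts the all-randomised primary analysis

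*Protocol article*

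**What the plan says.** Under Description of statistical methods in the protocol article, the primary logistic regression is tied to the full randomised set: "This analysis will include all livers randomised in an intention-to-treat (ITT) analysis". Later in the same section this is repeated: "An ITT analysis will be performed for the primary outcome and secondary (donor liver related) outcomes".

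Between these two statements, the article opens a second route. "A modified intention-to-treat analysis (mITT) will be considered for livers that were randomised but were not subsequently perfused", and "an independent adjudication panel will consider inclusions to a mITT analyses after consideration of these reasons, on a case-by-case basis". The only criterion offered for that judgement is that indirect logistical reasons may exist "rendering the inclusion of non-perfused livers to an ITT inappropriate, i.e. these reasons are not completely unrelated to the allocated intervention".

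Two other places bear on the same livers. The missing-data section {20c} states: "The primary outcome will be available for all livers randomised and perfused". Concealment mechanism {16b} states: "Randomised livers that are not perfused due to unforeseen reasons will not be replaced", and adds that non-perfusion should be very uncommon.

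**The concern.** A randomised unit can be omitted without disturbing the comparison only if the reason for omission could not have depended on its arm. A reason that is not completely unrelated to the intervention is at least partly related to it. The clause therefore names as grounds for omission the very situation in which omission can bias the comparison.

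The clause also refers to inclusion in an ITT, not only in an mITT, so it collides with the promise to analyse every randomised liver. The missing-data section does not resolve this, because it says nothing about the outcome of a randomised liver that was never perfused.

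The design gives the point some weight. Under Sequence generation {16a} and Implementation {16c}, the person who randomises also delivers the intervention and knows the allocation before perfusion starts. Under Intervention description {11a}, only the defatting arm receives the active filter and the added agents. Reasons linked to allocation are therefore conceivable, and with 30 livers per arm a few omissions would be visible in the result.

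**Working it through.** **The plan's own figure.** Sample size {14} gives 30 livers per arm, 65% meeting criteria on control, a 30-point difference (hence 95% on defatting), 5% significance and more than 80% power. I take the test as two-sided. With the pooled-variance formula and a mean proportion of 0.80:

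z = [0.30 × √30 − 1.96 × √(2 × 0.80 × 0.20)] / √(0.65 × 0.35 + 0.95 × 0.05) = (1.643 − 1.109) / 0.524 = 1.02, so power is 84.6%.

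The stated power reproduces. The sample size is not in question; the analysis set is.

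**Inputs for the check.** From the article: 30 per arm, with 65% and 95% taken as success rates among perfused livers. Assumed: k = 1 to 3 non-perfused livers, all in one arm (the article gives no number), and a non-perfused liver kept in the ITT counts as a failure (the article does not say so).

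**Risk difference.** With p the success rate among perfused livers in the affected arm, that arm's rate is p × (30 − k)/30 if the k livers are kept and p if they are dropped. Dropping them therefore raises that arm's rate by p × k/30:

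- defatting arm: 0.95/30 = 3.2 points per liver, towards defatting
- control arm: 0.65/30 = 2.2 points per liver, against defatting

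| k | Defatting-arm livers kept: rate, difference | Shift if dropped | Control-arm livers kept: rate, difference | Shift if dropped |
|---|---|---|---|---|
| 1 | 91.8%, 26.8 points | +3.2 | 62.8%, 32.2 points | −2.2 |
| 2 | 88.7%, 23.7 points | +6.3 | 60.7%, 34.3 points | −4.3 |
| 3 | 85.5%, 20.5 points | +9.5 | 58.5%, 36.5 points | −6.5 |

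The difference is 30.0 points in every row once the livers are dropped. If perfused livers succeed at 65% in both arms, the shift is 2.2, 4.3 and 6.5 points for k = 1, 2 and 3, in favour of whichever arm lost the livers.

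**Chance of a significant result for defatting.** This is an exact enumeration of the uncorrected chi-square test at two-sided 5%, as a simple stand-in for the planned logistic regression. With no losses it is 88%.

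- k = 1, 2, 3 lost from defatting: 76%, 60%, 44% if kept as failures; 89%, 87%, 86% if dropped.
- k = 1, 2, 3 lost from control: 92%, 94%, 96% if kept as failures; 88%, 87%, 87% if dropped.

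**The case against.** A reader might infer that the plan removes defatting failures from the primary analysis and so biases the main result towards defatting. The documents do not support that, for these reasons.

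- The all-randomised ITT is stated twice as the primary analysis. The mITT is only to be considered, and the panel rules on the mITT, not on the ITT. The section contradicts itself; it does not lay down a settled exclusion.
- The clause applies to either arm. Omitting control livers would work against defatting. Losses mainly in the defatting arm are plausible, since only that arm has the extra components, but no passage says so.
- The sentence begins from indirect logistical reasons, which makes a slip for completely unrelated quite possible. Failures of the filter or the added agents are not named as grounds for omission.
- Non-perfusion is expected to be very uncommon, so the realised effect may be nil. The sample size section also says that the trial is not mainly meant to demonstrate efficacy.

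Nor would the clause conceal a feasibility problem. Reasons for non-perfusion are to be documented, Declines and discards collects discard data with reasons from randomisation onwards, and the safety outcomes include discard rate and device failures. The auditing section's phrase "Livers excluded after randomisation due to factors not known at the time of randomisation" occurs in a definition of what is not a protocol deviation; it sets no analysis population. Whether the panel knows the arm, and how a non-perfused liver is scored, are details that a SAP could supply, so their absence from an article is not itself a fault. The worst-best-case analysis in the missing-data section could also bound such outcomes.

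All of this stands, and it limits the consequence. It does not rescue the wording. If the clause is a slip, it is still the only criterion that the article gives the panel, and it still contradicts the primary population.

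**Conclusion.** The point holds as a wrongly stated condition and an internal contradiction about the primary population, not as a demonstrated bias. As written, the clause permits omission of livers whose non-perfusion is linked to their arm. Neither the direction nor the number of such omissions can be known from the article.

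The size is conditional on two assumptions: perfused livers succeed at 65% and 95%, and a retained non-perfused liver counts as a failure. Each omitted liver is then worth about 3.2 points towards defatting or 2.2 points against it, on a planned difference of 30. One to three omissions in a single arm is an assumed range, and zero is quite possible. The wording should be settled before anyone sees outcomes by arm, because a later choice of reading could look result-driven.

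**What to change.** Revise the paragraph under Description of statistical methods, and repeat the same rule in the SAP:

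1. The primary ITT contains every randomised liver, and a liver that is not perfused counts as not meeting the functional criteria. This is a choice of estimand and should be labelled as one.
2. Use the worst-best-case analysis already described in the missing-data section as a sensitivity analysis for these livers, and amend that section to say what outcome a non-perfused liver receives.
3. Reverse the clause: an mITT, labelled supportive, may omit a non-perfused liver only if the panel, unaware of arm, judges the reason unrelated to allocation.
4. Report non-perfused livers by arm, with reasons.

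The cost is one paragraph of text and a masked summary of reasons for a panel that is already planned. The drawback is that the success rate in an arm with non-perfused livers may look slightly less favourable.

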### Criteria for discontinuing or modifying allocated interventions {11b}

The randomised entity in this study is the donor liver. Randomised livers that are not perfused due to unforeseen reasons will not be replaced. It is anticipated that non-perfusion of a randomised liver will be a very uncommon event

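### For very rare or early recipient outcomes, the logistic and Cox models named for secondary endpoints may not yield the promised effect size with a 95% interval

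*Protocol article*

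**What the plan says.** Under Description of statistical methods, the protocol article assigns models to secondary endpoints by outcome type: linear regression for continuous outcomes, then "logistic regression for binary outcomes; and Cox regression analysis for time to event outcomes". Counts and proportions are planned as well. Testing of secondary endpoints is to be very limited. The stated focus is on "presenting the effect size of the defatting + NMP intervention relative to standard NMP with 95% confidence interval", to inform a later definitive trial.

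Recipient outcomes are analysed in the "modified intention-to-treat (mITT) population of all livers randomised and transplanted, analysed according to randomised treatment".

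Penalised estimation appears once in that section. An additional model of the primary endpoint, adjusted for transplant centre and to be considered if counts allow, would use Firth's "penalised maximum likelihood to mitigate for small sample bias and overfitting".

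Under Secondary outcome measures, PNF is confined to the first 10 days. Graft and patient survival are reported at day 7, day 30, month 3 and month 6. No expected rate for any of these events in trial recipients is given.

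**The concern.** The trial is small, and the recipient analyses use only the livers that are transplanted. With rare events and so few recipients, one arm or both may have no event. The maximum-likelihood odds ratio or hazard ratio is then zero, infinite or undefined, and its Wald interval carries no information.

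This matters because the comparative interval is the stated purpose of the secondary analyses, and confirming safety is part of the primary objective. PNF and early graft loss or death are central to safety. They are also the outcomes for which the named method is most likely to fail to give the named result.

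**Working it through.** **The plan's own figure.** Sample size {14} states that "a sample size of 60 livers (30 per group) will provide greater than 80% power" for 65% against 95% at 5% significance. The article does not state sidedness, so two-sided is assumed. With the pooled normal approximation:

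- SE under no difference: √(2 × 0.80 × 0.20 / 30) = 0.1033
- SE under the alternative: √((0.65 × 0.35 + 0.95 × 0.05) / 30) = 0.0957
- z = (0.30 − 1.96 × 0.1033) / 0.0957 = 1.02, so power is about 84.6%

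This agrees with the plan. The point below does not affect the primary endpoint.

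**Number of recipients.** The ceiling is 30 per arm. If transplantation followed the planning rates for the functional criteria, the arms would have 30 × 0.65 = 19.5 and 30 × 0.95 = 28.5 recipients, taken as 20 and 28. This is an assumption, because the article leaves the decision to transplant with the surgeon.

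**Chance of an empty arm.** With the same event rate p in both arms,

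P(at least one arm with no event) = (1−p)^n0 + (1−p)^n1 − (1−p)^(n0+n1).

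For p = 3% with 20 and 28: 0.544 + 0.426 − 0.232 = 0.738. For p = 3% with 30 and 30: 0.401 + 0.401 − 0.161 = 0.641.

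| Assumed rate | 20 vs 28 | 25 vs 25 | 30 vs 30 | Expected events (20 vs 28) |
|---|---|---|---|---|
| 1% | 0.96 | 0.95 | 0.93 | 0.5 |
| 2% | 0.86 | 0.84 | 0.79 | 1.0 |
| 3% | 0.74 | 0.72 | 0.64 | 1.4 |
| 5% | 0.51 | 0.48 | 0.38 | 2.4 |
| 10% | 0.17 | 0.14 | 0.08 | 4.8 |
| 15% | 0.05 | 0.03 | 0.015 | 7.2 |

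With unequal rates of 10% (control, n = 20) and 5% (defatting, n = 28): 0.122 + 0.238 − 0.122 × 0.238 = 0.33.

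These figures include the case where both arms are empty. With 20 and 28 recipients, that part is 0.62 at 1%, 0.23 at 3% and 0.09 at 5%.

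**What the models return.** Take 0 of 28 against 2 of 20 as an illustration:

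- Ordinary logistic regression did not converge: log odds ratio about −27, SE about 5 × 10^5.
- Ordinary Cox regression: log hazard ratio about −27, SE about 5 × 10^5.
- Firth logistic regression: odds ratio (0.5/28.5) / (2.5/18.5) = 0.13, Wald 95% interval about 0.006 to 3.0.
- Risk difference, Newcombe: the Wilson limits are 0 to 0.121 for 0/28 and 0.028 to 0.301 for 2/20. The difference is −0.10, with lower limit −0.10 − (0.301 − 0.10) = −0.30 and upper limit −0.10 + √(0.121² + 0.072²) = +0.04.

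The last two give a finite interval; the first two do not.

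**The case against.** The strongest objection is that this belongs in the statistical analysis plan, which the article cites and which is not shown. Naming a model family by outcome type is normal in a protocol, and a fallback for sparse data is commonly left to the later document. That stands as a reason to keep the point minor: the absence of a fallback is not in itself an error. It does not remove the point, because the article names both a method and an output, and the one can fail to deliver the other.

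Three stronger readings are tempting but not supported:

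- That ordinary models are fixed for graft loss, death and PNF in particular. The sentence is generic and names none of them. Nor does it specify Wald intervals; a profile-likelihood interval can still give a one-sided bound when one arm is empty.
- That an empty arm is likely for all three outcomes. The article gives no rates. It reports immediate function in all 22 transplanted livers of a selected earlier series, which fits low early rates, but it also cites a 71% higher risk of graft loss with moderate to severe steatosis. For 6-month graft loss or death, an empty arm is possible but not shown to be likely.
- That the plan sees the problem and withholds the remedy. Firth's method is justified there by small-sample bias and overfitting when centre is added; empty arms are not mentioned.

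It is also true that counts and proportions by arm are planned, so the raw information survives, and that with so few events no method gives a precise answer. What is lost is the promised comparative interval.

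**Conclusion.** The point holds as a minor one, limited to very rare or early recipient outcomes: PNF, and graft loss or death by day 7 or day 30. At an assumed event rate of 1% to 3%, at least one arm is more likely than not to be empty, with a chance of about 64% to 96% across 20 vs 28 and 30 vs 30 recipients. At 5% it is about 38% to 51%, and at 10% about 8% to 17%. When it happens, the ordinary odds or hazard ratio has no finite estimate or usable Wald interval.

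The result rests on assumed event rates, taken as equal in the two arms except where stated, and on an assumed number of transplants below the ceiling of 30 per arm. If the analysis plan already names a sparse-data method, only the wording of the article needs to be aligned with it.

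**What to change.** Add one sentence to the statistical methods section or the analysis plan. For sparse recipient outcomes, report the proportion in each arm and the risk difference with a 95% interval valid for sparse data (Miettinen-Nurminen or Newcombe). For graft and patient survival, do this at the four times already fixed. Where there is censoring, use Kaplan-Meier estimates, with single-arm limits that do not collapse when an arm has no event, as Greenwood's variance does. Give odds or hazard ratios only from Firth-penalised models with profile-likelihood intervals, and give no hazard ratio if neither arm has an event.

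No further data are needed. The cost is that penalised estimates are shrunk toward no effect, perhaps noticeably at very low counts, and the intervals will be wide, as the illustration shows.

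The gain is an interval that exists and can be carried into the design of the next trial.
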